**Figure 2 F2:**
[figure not shown]
Classification of incisional hernias according tot the European Hernia Society.

Postoperatively: open or laparoscopic/length of the scar/duration of surgery/type of mesh used/size of the mesh/type of mesh fixation/presence of bleeding/accidental bowel lesion/use of tubes/use of per-operative antibiotics/possible re-operation.

Inpatient: daily VAS score/use of analgesics/length of hospital stay/morbidity/mortality/QOL at two days post-surgery.

During Follow-up at 2 weeks and 3 months: healthcare and lost productivity costs/QOL at 2 weeks and 3 months post-surgery will be measured through the Short Form 36 and the Carolina Comfort Scale/time to return to work/recurrence/pain/wound infection/patient satisfaction/other morbidity.

During long-term follow-up at 1, 3 and 5 years: Recurrence/pain/wound infection/patient satisfaction/other morbidity.

**Primary outcomes** are:

Length of hospital stay. This is the time until discharge. A patient can be discharged when he/she is able to move normally, tolerate a normal diet and has a VAS painscore < 5 without the use of opiates.

Quality of life measures through SF-36 and CCS.

**Secondary endpoints** are:

Re-operation rate for recurrence or complications of the incisional hernia repair. The analysis will be continued after the cost-effectiveness study has ended, a longer follow-up is needed to examine the recurrence-rate.

28 days post surgery morbidity and mortality,

Total mean costs will be related to the following effect measures in the cost-effectiveness analyses:

1) Time to full recovery.

2) Quality-adjusted life-years (QALYs) based on the SF-36D
[11].

Intention to treat analysis will be performed. Blinding is impossible as the surgical difference is visible from the outside.

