### Analysis of cost-effectiveness

The analysis will be done according to the intention-to-treat principle. Missing cost and effect data will be imputed using multiple imputations according to the MICE algorithm developed by Van Buuren
[13]. Costs typically have a highly skewed distribution. Policy makers want to have information on the difference in mean total costs between the two treatment-groups to be able to estimate the total health care budget needed for a specific condition
[14]. Therefore, bias-corrected and accelerated bootstrapping with 5000 replications will be used to calculate 95% confidence intervals around the mean difference in total costs between the treatment groups. Incremental cost-effectiveness ratios (ICERs) will be calculated by dividing the difference in mean total costs between the treatment groups by the difference in mean effects between the treatment groups. Bootstrapping will be used to estimate the uncertainty surrounding the ICERs, which will be graphically presented on cost-effectiveness planes. Cost-effectiveness acceptability curves and net monetary benefits will also be calculated. Cost-effectiveness acceptability curves show the probability that collaborative care is cost-effective in comparison with usual care for a range of different ceiling ratios thereby showing decision uncertainty
[15].

The baseline data of both treatment groups will be described and 95% confidence intervals will be calculated. Additional as-treated analyses will be done, because patients who were planned to have a laparoscopic repair might have had an open correction and vice versa. Differences in primary and secondary endpoints between the two treatment groups will be calculated as well as their 95% confidence intervals. Student’s t tests, Chi square tests or Fisher exact tests will be applied where appropriate. The risk of re-operation will also be studied by application of a multiple logistic regression model.

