### Statistics

*Sample size calculation*: This is a superiority design: Our hypothesis is that length of hospital stay is shorter after incisional hernia repair, and therefore the laparoscopic approach will be superior in terms of cost-effectiveness. Statistics are based on an average hospital stay of 2 days (SD 5) after laparoscopic repair
[8]. The outcome is considered superior if there is a difference in hospital stay of more than 2 days. Therefore, 135 patients in each treatment arm are needed (alpha 0,05/power 0,9)
[16]. Loss to follow-up may occur; we will therefore aim for an inclusion of 300 patients.

*Randomisation* will be performed through a computer-guided system. A stratified block-randomisation will be used per centre. The randomisation code will be noted on the patients file. Peritonitis carcinomatosa, unplanned surgical procedures for pathology that was not discovered during pre-operative analysis, absence of an incisional hernia are reasons for post-randomization exclusion.

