### Time schedule

Study preparation and formation of a core study group is already in progress. Initiation of the INCH-trial around 1-8-2012 after METC permission is obtained in each hospital. We aim for an inclusion rate of 10-15 patients per month. About 28 months are needed to include the amount of patients needed to calculate the difference in length of hospital stay. After this period the trial will continue; to meet the secondary end-point a longer follow-up period is needed. The follow-up will be continued at 3 and 5 year after index surgery. Patients who don’t want to participate and patient who are excluded will be registered.

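### Re-operation is followed for up to 5 years with loss expected, but the methods named for it ignore time at risk and no horizon is fixed

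*Protocol article*

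**What the plan says.** All references are to the protocol article.

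- **Endpoint** (Case record form, secondary endpoints): "Re-operation rate for recurrence or complications of the incisional hernia repair". This mixes early events (complications) with late ones (recurrence). No time point is attached.
- **Need for longer observation** (same place): "The analysis will be continued after the cost-effectiveness study has ended, a longer follow-up is needed to examine the recurrence-rate".
- **Visits** (Case record form): "During long-term follow-up at 1, 3 and 5 years: Recurrence/pain/wound infection/patient satisfaction/other morbidity". The Time schedule section adds "The follow-up will be continued at 3 and 5 year after index surgery" and links the longer follow-up to the secondary endpoint. It puts accrual at about 28 months.
- **Methods** (Analysis of cost-effectiveness): differences between groups with 95% confidence intervals, and "Chi square tests or Fisher exact tests will be applied where appropriate". Then: "The risk of re-operation will also be studied by application of a multiple logistic regression model". No time-to-event method is named.
- **Loss** (Statistics): "Loss to follow-up may occur", which is why the target is raised from 270 to 300 patients.
- **Missing data** (Analysis of cost-effectiveness): multiple imputation for cost and effect data. The Economic evaluation section sets its horizon at 3 months.
- **Death** (Exclusion criteria): only a life expectancy below one year excludes a patient on this ground, so deaths before 3 or 5 years are possible.

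**The concern.** A chi-square test, a Fisher test and a logistic model all need a yes/no status for every patient over one common window. Over 5 years some patients will be lost without a re-operation, and their status at the end of the window is unknown. These methods cannot use the part of the window in which such a patient was observed. Coding the patient as not re-operated pulls the risk down. Dropping the patient pushes it up, because patients whose event was seen before they could be lost stay in.

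Re-operation and recurrence show whether a shorter hospital stay is bought at the price of a less durable repair. A reader will want the risk in each arm at a stated time, and that absolute risk is what the named methods handle least well.

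**Working it through.** **1. The plan's own figures.** The only design figures concern hospital stay. With a difference of 2 days, SD 5, two-sided alpha 0.05 and power 0.90, n per arm = 2 × (1.960 + 1.282)² × 5² / 2², about 132, close to the stated 135. The margin for loss is 1 − 270/300 = 10%, not tied to any time point. No re-operation rate and no loss rate at 1, 3 or 5 years is given, so the inputs below are assumptions.

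**2. Assumptions.** True 5-year re-operation risk R = 10% or 20%. Loss L by 5 years = 10%, 20% or 30%, for reasons other than death and unrelated to re-operation. Constant hazards.

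**3. Formulas.** Let a = −ln(1 − R) and b = −ln(1 − L).

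- Lost patients coded as no event: crude = a/(a + b) × [1 − (1 − R)(1 − L)]
- Lost patients dropped: complete-case = crude / [crude + (1 − R)(1 − L)]

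Example, R = L = 20%: a = b, so crude = 0.5 × (1 − 0.64) = 18.0%, and complete-case = 0.18/(0.18 + 0.64) = 22.0%.

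| True risk | Loss | Coded as no event | Dropped |
|---|---|---|---|
| 10% | 10% | 9.5% | 10.5% |
| 10% | 20% | 9.0% | 11.1% |
| 10% | 30% | 8.4% | 11.8% |
| 20% | 10% | 19.0% | 20.9% |
| 20% | 20% | 18.0% | 22.0% |
| 20% | 30% | 16.9% | 23.2% |

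In relative terms the crude risk is about 5% (9.5 against 10) to 16% (8.44 against 10) too low. The complete-case risk is about 5% to 18% (11.81 against 10) too high. An estimator that censors at last contact would target the true value under these assumptions.

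**4. Arm contrast, equal loss.** Control risk 20% and hazard ratio 0.5 give a risk of 1 − 0.8^0.5 = 10.6% in the other arm. The odds ratio is (0.1056/0.8944)/(0.20/0.80) = 0.472 without loss. With 30% loss in both arms, coded as no event, it is 0.480.

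**5. Arm contrast, unequal loss, no true effect.** Loss 10% in one arm and 30% in the other, coded as no event:

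- R = 20%: (0.1693/0.8307)/(0.1902/0.8098) = 0.87
- R = 10%: (0.0844/0.9156)/(0.0950/0.9050) = 0.88

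If lost patients are dropped instead, the error changes direction. For R = 20%: (0.2322/0.7678)/(0.2090/0.7910) = 1.14.

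**6. No loss.** With a fixed 5-year window and complete follow-up, the crude proportion equals the true risk (20.0% for R = 20%). If the data were instead cut on the calendar day when the last patient reaches 1 or 3 years, with 28 months of even accrual, the crude proportion would be 9.2% or 16.9% where the 5-year risk is 20%.

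**The case against.** **Death.** One might infer that every patient who dies without a re-operation is misclassified. That does not hold. At a fixed horizon such a patient did not have a re-operation, and counting no event gives the correct cumulative incidence. If the 20% loss in the worked example were all deaths, 18.0% would be the right answer. The table therefore applies to loss other than death.

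**Unequal follow-up.** The staggered entry invites the reading that patients will be analysed over different windows. The visits are set at fixed times after surgery, and no calendar cut-off is planned. The 9.2% and 16.9% show only what an unfixed horizon would allow.

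**Certainty and size.** A reader might conclude that the logistic model must give a wrong risk. With complete follow-up at a fixed time it is valid. At 10% loss, the only margin the article mentions, the error is about one percentage point or less. Nothing in the article suggests that loss will differ by arm, although the surgery is unblinded, so a difference cannot be excluded.

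**Imputation.** The imputation rule shares a heading with the logistic model and might be read to cover re-operation. This is doubtful: the effect measures listed for the cost-effectiveness analyses are time to full recovery and quality-adjusted life-years, over 3 months.

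**Role.** The model is supplementary, on a secondary endpoint that includes early re-operations, for which it is suitable. The long-term visit list names recurrence, not re-operation. All this is true, but the companion tests share the limitation, and re-operation for recurrence is part of the endpoint.

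**Detail for a SAP.** A horizon and a rule for losses may stand in a SAP that is not shown, and their absence alone would be no finding. The point rests on the methods that the article does name.

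**Conclusion.** The point holds in a limited form. The article extends follow-up to 5 years, expects loss, and says that "a longer follow-up is needed to examine the recurrence-rate", yet every method it names for re-operation disregards time at risk, and it fixes no horizon. The absolute long-term risk can be misestimated by about 5-16% downwards or 5-18% upwards in relative terms. These figures rest on assumed 5-year risks of 10% and 20%, constant hazards and 10-30% non-informative loss by 5 years. The treatment comparison is at risk mainly if loss differs by arm. Under the assumed 10% versus 30%, the odds ratio is 0.87-0.88 with lost patients coded as no event, or about 1.14 with them dropped, where the truth is 1. The primary endpoint is not touched. The change is still worth making, because the stated method can be replaced by a better one at little cost.

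**What to change.** - Define the endpoint as time from index surgery to first re-operation for recurrence or complications. Censor at last contact and treat death as a competing event.
- Show cumulative incidence curves by arm, with the 1-, 3- and 5-year risks and their 95% confidence intervals.
- Compare the arms with a time-to-event model, such as a cause-specific Cox model, with treatment and few pre-specified covariates. At the assumed risks of 10-20%, 300 patients yield only about 30 to 60 events (0.10 × 300 to 0.20 × 300).
- Keep the logistic model and the chi-square or Fisher test for an early fixed horizon with nearly complete follow-up, such as 3 months.
- Report loss by arm. The time-to-event analysis also assumes that loss is unrelated to re-operation, so a clear imbalance calls for a sensitivity analysis.

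Cost: a change of wording in the analysis section, and recording of the dates of re-operation, death and last contact. No change to sample size, visits or treatment.

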### Statistics

*Sample size calculation*: This is a superiority design: Our hypothesis is that length of hospital stay is shorter after incisional hernia repair, and therefore the laparoscopic approach will be superior in terms of cost-effectiveness. Statistics are based on an average hospital stay of 2 days (SD 5) after laparoscopic repair
[8]. The outcome is considered superior if there is a difference in hospital stay of more than 2 days. Therefore, 135 patients in each treatment arm are needed (alpha 0,05/power 0,9)
[16]. Loss to follow-up may occur; we will therefore aim for an inclusion of 300 patients.

*Randomisation* will be performed through a computer-guided system. A stratified block-randomisation will be used per centre. The randomisation code will be noted on the patients file. Peritonitis carcinomatosa, unplanned surgical procedures for pathology that was not discovered during pre-operative analysis, absence of an incisional hernia are reasons for post-randomization exclusion.

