**Methods/Design:**

A randomized multi-center clinical trial comparing cost-effectiveness of open and laparoscopic repair of incisional hernias. Patients with a symptomatic incisional hernia, eligible for laparoscopic and open incisional hernia repair. Only surgeons, experienced in both open and laparoscopic incisional hernia repair, will participate in the INCH trial. During incisional hernia repair, a mesh is placed under or on top of the fascia, with a minimal overlap of 5 cm. Primary endpoint is length of hospital stay after an incisional hernia repair. Secondary endpoints are time to full recovery within three months after index surgery, post-operative complications, recurrences, mortality and quality of life.

Our hypothesis is that laparoscopic incisional hernia repair comes with a significant shorter hospital stay compared to open incisional hernia repair. A difference of two days is considered significant. One-hunderd-and-thirty-five patients are enrolled in each treatment arm. The economic evaluation will be performed from a societal perspective. Primary outcomes are costs per patient related to time-to-recovery and quality of life.

The main goal of the trial is to establish whether laparoscopic incisional hernia repair is superior to conventional open incisional hernia repair in terms of cost-effectiveness. This is measured through length of hospital stay and quality of life. Secondary endpoints are re-operation rate due to post-operative complications or recurrences, mortality and quality of life.

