### Case record form

*At first presentation* in the outpatient clinics: age/sex/co-morbidity/pre-illness/working-social activities/surgical history/symptoms of the incisional hernia/classification of the incisional hernia:

The European Hernia Society (EHS) tried to categorize incisional hernias, in order to be able to compare different scientific incisional hernia research
[10]. A classification system of abdominal wall hernias was formulated (Figure 
2). This classification will be used in the INCH-trial.

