### Feasibility

Twelve hospitals, both university medical centres and community hospitals, will participate in this trial. The study group consists of hernia experts from these 12 centres, who frequently perform laparoscopic as well as open hernia surgery. These hospitals perform about 20-30 incisional hernia corrections a year, and aim for an inclusion of 10-15 patients each year.

We aim for 125 patients per year, hence 12-13 inclusions every month. This is highly feasible, because these 12 centres together perform over 300 incisional hernia repairs annually. We aim for participation of more centres along the way, but only experienced laparoscopic surgeons can participate.

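### Randomisation is stratified by centre but the named comparisons ignore centre: a conservative mismatch that costs some precision if centre predicts length of stay

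*Protocol article*

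**What the plan says.** Under Statistics, the allocation method is fixed: "A stratified block-randomisation will be used per centre". Under Feasibility: "Twelve hospitals, both university medical centres and community hospitals, will participate in this trial". The same section hopes that further centres will join.

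The comparisons are set out under Analysis of cost-effectiveness: "Differences in primary and secondary endpoints between the two treatment groups will be calculated as well as their 95% confidence intervals", followed by "Student’s t tests, Chi square tests or Fisher exact tests will be applied where appropriate". The only clinical-endpoint model concerns a secondary endpoint, and its covariates are not named: "The risk of re-operation will also be studied by application of a multiple logistic regression model".

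The abstract makes length of hospital stay the primary endpoint. Nowhere does the article use centre as a stratum, covariate or random effect in an analysis.

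**The concern.** Blocking within centre keeps the arms close to balanced inside each hospital, so differences in average stay between hospitals largely cancel out of the treatment contrast. A pooled t test does not use this. It leaves the between-centre variance in its error term and reports a standard error larger than the true sampling variability of the estimate. The same reasoning applies to the unstratified tests for binary endpoints.

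A centre effect on stay is plausible here. The hospitals are a mix of university and community centres, and under Treatment the open technique and the choice and fixation of mesh are left to the surgeon or surgical team. At stake is precision on the primary endpoint: an interval wider than the design warrants and a test with less power than the same data could give.

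**Working it through.** **Inputs from the protocol article (Statistics, Feasibility):** SD 5 days; difference 2 days; alpha 0.05; power 0.90; 135 per arm; 12 centres. Sidedness is not stated. **Assumed:** the share ρ of the variance in stay that is due to centre, taken over 0% to 20% because the article gives none.

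**Step 1: reproduce the sample size.** Two-sided normal approximation: n = 2 × (1.960 + 1.282)² × 5² / 2² = 132 per arm after rounding up. The noncentral t version gives 133. A one-sided test would give 108, so the plan is two-sided in effect. The stated 135 is reproduced closely and gives power 0.908.

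**Step 2: standard errors.**
- Reported by the unadjusted t test: 5 × √(2/135) = 0.609 days.
- True value under 1:1 blocking within centre, which is also what a model with centre reports: 5 × √(1 − ρ) × √(2/135).
- Ratio of reported to true: 1/√(1 − ρ).

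**Step 3: error rate and power.** With Φ the standard normal distribution function and 2/0.6086 = 3.286:
- Actual type I error, unadjusted: 2 × [1 − Φ(1.960/√(1 − ρ))].
- Actual power, unadjusted: Φ[(3.286 − 1.960)/√(1 − ρ)].
- Power with centre in the model: Φ[3.286/√(1 − ρ) − 1.960].

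| Assumed centre share | SE with centre (days) | Unadjusted SE too large by | Type I error, unadjusted | Power, unadjusted | Power, with centre | Power forgone (points) |
|---|---|---|---|---|---|---|
| 0% | 0.609 | 0% | 5.0% | 0.908 | 0.908 | 0 |
| 2% | 0.602 | 1.0% | 4.8% | 0.910 | 0.913 | 0.3 |
| 5% | 0.593 | 2.6% | 4.4% | 0.913 | 0.921 | 0.8 |
| 10% | 0.577 | 5.4% | 3.9% | 0.919 | 0.934 | 1.5 |
| 20% | 0.544 | 11.8% | 2.8% | 0.931 | 0.957 | 2.6 |

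**Step 4: check by simulation.** 10,000 trials per scenario, 270 patients over 12 centres, blocks of four, normal outcome.
- Share 10%: the t test reports a mean SE of 0.606 against an actual SD of the estimate of 0.581. Type I error is 4.1% unadjusted and 5.2% with centre; power is 91.8% and 93.1%.
- Share 20%: 0.603 against 0.545. Type I error is 3.0% and 4.9%; power is 92.7% and 95.3%.
- Share 0%: the two analyses agree (type I error 5.0% for both; power 90.8% and 90.7%), so a centre term that turns out to be unnecessary costs almost nothing.

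**The case against.** **The loss depends on a number that the article does not give.** This stands. With no centre effect there is no loss, and at a share of 2% to 5% it is small.

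**The larger shares sit awkwardly with the protocol's own figures.** With SD 5, a share of 10% means a between-centre SD of √0.10 × 5 = 1.58 days, and 20% means 2.24 days, against an assumed laparoscopic mean of 2 days. Under additive normal centre effects, about 10% and 19% of centres would then have a negative mean stay. A mean of 2 with SD 5 also implies strong skew, so much of the variance may come from a few long individual stays. The Case record form section sets common discharge criteria as well, which should narrow differences between hospitals, although they say when a patient may leave, not when the patient must. This favours the lower half of the table without removing the effect.

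**An article condenses, and a separate analysis plan may adjust for centre.** That is possible, and the article does qualify its list of tests. But it is not silent: it names tests that do not match the randomisation it also names. An analysis plan that adjusts would depart from the published tests, so the two should be reconciled in writing. The logistic model for re-operation may already contain centre, so the point is firm only for the crude differences and the named tests.

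**Stronger readings that the article does not support.** A reader might infer that the trial is underpowered, that its false-positive rate is too high or that its estimate is biased. None of these follows: unadjusted power is 0.908 or more in every row, the error is conservative, and the treatment contrast is unbiased. A reader might also infer that leaving the hernia classification and other baseline data out of the primary comparison is an error. The article says of that classification "This classification will be used in the INCH-trial", but allocation is not stratified on it, so an unadjusted analysis is legitimate in that respect.

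**Conclusion.** The point holds in a limited form. The analysis named in the article omits the factor on which randomisation is stratified. If centre predicts stay, intervals are too wide and tests are conservative. At centre shares of 2% to 10% the standard error is 1.0% to 5.4% too large and 0.3 to 1.5 points of power are forgone. A share of 20% gives 11.8% and 2.6 points but is hard to square with a mean stay of 2 days.

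The direction follows from the design. The size rests on the assumed centre share, on SD 5 and 135 analysed patients per arm, and on 1:1 blocking that keeps each centre nearly balanced. The error rates and power also use a normal approximation and were not checked for a skewed outcome. The plan as written is valid but not fully efficient. The weight is minor to moderate, and the case for acting is that the gain is free.

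**What to change.** - **Primary endpoint:** estimate the difference in days from a model that includes centre as a fixed or random effect, with very small centres pooled by a rule set in advance. A centre-stratified rank test would not be a substitute, because superiority is defined as a difference in days.
- **Binary endpoints:** use a centre-stratified method such as Mantel-Haenszel where events allow. For rare events such as 28-day mortality, a model with 12 or more centre terms may be unstable, so state the fallback in advance.
- **Costs and cost-effectiveness ratios:** draw bootstrap resamples within centre and arm. The article does not say how resamples are drawn, so this completes the text and does not correct it.
- **Optional:** pre-specified baseline covariates could add precision, but they are not part of this correction.

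The cost is a few sentences, settled before outcomes are compared by arm. That timing also rules out a later choice between adjusted and unadjusted results. No new data or patients are needed, and the sample size stands.

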### Inclusion criteria

The following patients will be eligible for the randomization to either open or laparoscopic repair: Adult patients who are referred to the surgical clinic for assessment of an incisional hernia, either primary or recurrent. Imaging of the abdomen will only be done when it is unclear whether an incisional hernia is present. The need for surgery will be determined; pain, severe discomfort and episodes of visceral incarceration are indications for surgery. Only symptomatic patients will get a surgical correction of the incisional hernia. Patients whose incisional hernia is suitable for laparoscopic repair are included in the trial, this decision is at the discretion of the surgeon. After consenting to the study, the patient will be randomized to either open or laparoscopic repair. Patients who are excluded or who don’t want to participate will be registered. (Figure 
1; flowchart).

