### Treatment

Patients will be randomized, using a computer-program, to one of the following surgical approaches:

I) **Open repair** of the incisional hernia: the employed open technique is at the discretion of the participating surgeon. There is no evidence, which open technique, is best; bridging as well as augmenting techniques might be used. Onlay, sublay as well as CST technique are allowed as long as a mesh is used. An overlap of at least 5 cm of the mesh over the fascia is preferable.

II) **Laparoscopic repair** of incisional hernias will entail employment of mesh that is placed subfascially with a minimal overlap of 5 cm. Choice and fixation of the mesh is at the discretion of the surgical team. During laparoscopic surgery a photograph will be taken of the hernia defect before and after the correction is done. When laparoscopic repair is not successfully achieved or complications occur, the surgeon may decide to change to the open surgical procedure (i.e. conversion); this is common practice in laparoscopic surgery.

In each approach, the use of a mesh is preferable, as this has shown to reduce the recurrence-rate
[9]. Every detail of the technique should be described. Dutch hernia experts will perform the surgical corrections.

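### Exclusions after randomisation, for findings that mostly emerge at the allocated operation, contradict the promised intention-to-treat analysis and can bias length of stay and costs

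*Protocol article*

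**What the plan says.** The protocol article makes two kinds of statement about who is analysed.

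- **Everyone, as allocated.** The outcomes text under Case record form (after Figure 2) says "Intention to treat analysis will be performed". The section Analysis of cost-effectiveness says "The analysis will be done according to the intention-to-treat principle". Neither statement is qualified.
- **Not everyone.** The randomisation paragraph under Statistics lists peritoneal carcinomatosis and continues: "unplanned surgical procedures for pathology that was not discovered during pre-operative analysis, absence of an incisional hernia are reasons for post-randomization exclusion".

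Four other statements determine when and how these findings arise:

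- Inclusion criteria: "After consenting to the study, the patient will be randomized to either open or laparoscopic repair". Allocation therefore comes before surgery.
- Inclusion criteria: "Imaging of the abdomen will only be done when it is unclear whether an incisional hernia is present".
- Case record form: "Blinding is impossible as the surgical difference is visible from the outside".
- Treatment, on the open arm: "Onlay, sublay as well as CST technique are allowed as long as a mesh is used".

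The primary outcome that the exclusions would affect is "Length of hospital stay. This is the time until discharge". Inclusion criteria and Time schedule say that excluded patients are registered. They do not say that these patients are followed or analysed.

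**The concern.** An intention-to-treat comparison is protected by randomisation because nothing that happens after allocation decides who is counted. The exclusion rule gives up that protection in three ways.

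1. With allocation before surgery and imaging only in doubtful cases, carcinomatosis, unexpected disease or a missing hernia will mostly be discovered at the allocated operation. The article does not say when, or by whom, these reasons are judged, or that they are judged without knowledge of the arm.
2. An extra procedure for unexpected disease is not a baseline trait. It is a decision taken after allocation, and it can change both length of stay and costs.
3. The two operations need not reveal the same things. Laparoscopy inspects the abdominal cavity, whereas an onlay repair, which the open arm permits, need not enter it. This is a clinical inference and not a statement in the article, but it makes arm-dependent detection possible.

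The rule also sits badly with conversion. Under Treatment, a laparoscopic case may be converted to open surgery, and the analysis text keeps such patients by allocation, with an additional as-treated analysis. A patient converted because of unexpected disease who also has an extra procedure is kept by one part of the article and dropped by another.

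At stake is the composition of the primary analysis set, and with it the length-of-stay and cost comparisons.

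**Working it through.** **1. The plan's own figure.** Inputs from Statistics: difference 2 days, SD 5, alpha 0.05, power 0.90.

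n per arm = 2 × (1.960 + 1.282)² × 5² / 2² = 131.3, so 132; the t-test version gives 133. The stated 135 is reproduced as a two-sided calculation (one-sided would give 108). The total of 300 is 270 / (1 − 0.10). Sample size is not in dispute.

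**2. Bias when there is no true difference.** The article gives no frequency, split by arm or length of stay for these cases, so all of the following are assumptions. A share p of each arm has an excluding finding and stays L days longer. The rule removes a fraction f of them in that arm.

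Mean of retained patients = base + p(1 − f)L / (1 − pf)

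With f = 1 in the laparoscopic arm, its retained mean is the base. The spurious difference (open minus laparoscopic) is therefore the second term for the open arm. The rejection rate uses a standard error of 5 × √(2/135) = 0.61 day and a nominal 5% level.

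| p | L (days) | f, open | Spurious difference (days) | Rejection rate |
|---|---|---|---|---|
| any | any | 1 | 0.00 | 5.0% |
| 2% | 5 | 0.5 | 0.02 × 0.5 × 5 / 0.99 = 0.05 | 5.1% |
| 5% | 10 | 0.5 | 0.05 × 0.5 × 10 / 0.975 = 0.26 | 7.1% |
| 2% | 5 | 0 | 0.02 × 5 = 0.10 | 5.3% |
| 5% | 10 | 0 | 0.05 × 10 = 0.50 | 13.0% |

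If detection is higher in the open arm, the sign reverses: f = 0.5 laparoscopic and 1 open gives −0.05 to −0.26 day.

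**3. Shift when the planned effect is true.** Assume mean stays of 2 and 4 days for ordinary laparoscopic and open patients, and 10 days for those with the finding. All are detected at laparoscopy, and a share y of the open arm is detected and excluded.

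- p = 5%, y = 2%. All randomised: 0.95 × (4 − 2) = 1.90. Equal exclusion: 2.00. Unequal exclusion: (0.95 × 4 + 0.03 × 10) / 0.98 − 2 = 2.18.
- p = 3%, y = 1%. All randomised: 0.97 × 2 = 1.94. Equal exclusion: 2.00. Unequal exclusion: (0.97 × 4 + 0.02 × 10) / 0.99 − 2 = 2.12.

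Of the total shifts of 0.28 and 0.18 day, 0.10 and 0.06 come from removing dilution, which happens even when detection is equal. Only 0.18 and 0.12 day come from unequal detection.

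**4. Power.** Normal approximation, 2-day difference, SD 5. With all 300 kept (150 per arm) power is 0.934. Excluding 2%, 5% or 10% leaves 0.929, 0.922 or 0.908.

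**The case against.** The strongest defence is that the three reasons are largely corrections of eligibility. A patient without a hernia never met the basic entry condition, and carcinomatosis was probably present at randomisation. Dropping patients for baseline traits does no harm between arms if the traits are found equally in both. Imaging is also done when the presence of a hernia is in doubt, which should make that exclusion uncommon. Much of this stands for two of the three reasons. It does not cover the extra procedure, which follows allocation, and the article does not ensure equal ascertainment for any of them.

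A second objection concerns the illustration. It gives undetected open patients a long stay, although the long stay may come from the extra procedure, which they would not have. If they stay 4 days, the first scenario in step 3 gives exactly 2.00 after exclusion, so the assumed repair effect is not inflated. This is correct. However, the all-randomised difference is then (0.95 × 4 + 0.03 × 4 + 0.02 × 10) − (0.95 × 2 + 0.05 × 10) = 4.12 − 2.40 = 1.72 days. The exclusion still gives a different answer from intention to treat.

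A reader might also infer three stronger claims that the documents do not support:

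- **That the rule favours laparoscopy.** No rates by arm and no mix of open techniques are given. Patients with no hernia may have short stays, and the sign depends on which arm detects more.
- **That the bias is 14% of the target (0.28 of 2 days).** That figure rests on assumed rates and includes the removal of dilution. The unequal-detection part of the same scenario is 0.18 day, or 9%, about 0.3 of a standard error.
- **That the exclusions use up the 30 patients added for loss to follow-up.** Power is still 0.908 with 10% excluded.

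**Conclusion.** The contradiction is on the page and needs no assumption: two unqualified intention-to-treat statements, one rule that removes randomised patients, and no modified set to reconcile them. Followed as written, the rule gives a primary comparison that is not the stated one.

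The bias is conditional. It is zero between arms if the findings are detected and acted on equally. Under the unequal detection assumed in step 2, it is roughly 0.05 to 0.5 day against a 2-day target, with a false-positive rate of 5.1% to 13.0%. Neither the size nor the direction is established by the article. That uncertainty is itself a reason to keep everyone in, because a bias of unknown sign cannot be corrected afterwards. The change should be made before analysis on the strength of the contradiction; the illustrated magnitude alone would not compel it.

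**What to change.** Replace the exclusion sentence under Statistics with text to this effect:

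> All randomised patients are analysed in the arm to which they were allocated. Length of stay is counted from the index operation to discharge, whether or not a hernia was found or repaired. Patients with peritoneal carcinomatosis, an unplanned procedure for unexpected disease, or no hernia found remain in the primary analysis and are reported with reasons by arm. They are left out only in a named sensitivity analysis.

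The counting rule is needed because the Abstract ties the endpoint to stay following a hernia repair, which has no meaning when no repair was done. Ideally, membership of the sensitivity set is judged without knowledge of the arm. The text should also say that registered patients who were randomised are followed for outcomes.

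The cost is small. Length of stay and hospital cost data are already collected. Dilution is slight (0.10 and 0.06 day in the two scenarios of step 3) and the variance may rise a little. Under the planning SD, keeping all 300 gives power of 0.934, against 0.908 with 135 per arm.
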